### Ethics and dessimination

#### Ethical considerations

This Protocol has been designed to comply with the Declaration of Helsinki and any subsequent amendments, the ICH Guidelines for Good Clinical Practice (CPMP/ICH/153/95) annotated with TGA comments (July 2000), the NHMRC National Statement on Ethical Conduct in Research involving Humans (2007, updated 2018), the policies and procedures of any applicable local guidelines. The trial will be conducted in compliance with the Protocol, International Conference on Harmonisation, Good Clinical Practice (ICH GCP) Guidelines in Australia, and applicable regulatory requirements. Except for an emergency situation in which proper care for the protection, safety and well-being of the study participant requires that an alternative treatment be used, the study shall be conducted exactly as described in the approved protocol.

#### Safety and data monitoring

A Safety Monitoring Committee will be established for the trial, which will include:

Site PIs.Chief investigator.Head of Haematology.BiomeBank representative(s).

The Safety Monitoring Committee will meet quarterly and review recruitment rates, AE data and other logistical aspects of the trial (e.g. budget). When the Safety Monitoring Committee discussion concerns the treatment of individual participants, the Safety Monitoring Committee consultation process will include the treating clinician of the participant concerned. Participation by the trial statistician and BiomeBank representative will be optional. All discussions about a participant and/or their data, once they are enrolled, will be in a de-identified manner.

If the Safety Monitoring Committee identifies a serious Treatment Emergent Adverse Event (TEAE), they have the discretion to stop the trial or withhold the Investigational Product from the participant. This will be discussed and determined by the Safety Monitoring Committee depending on the severity of the TE-AE and its relationship with the Investigational Product.

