#### Preparation of FMT

Donor stool will be sourced from healthy volunteers and rigorously screened for infections, antibiotic resistant bacteria, and all other criteria specified by the Australian Therapeutic Goods Administration (TGA) [17]. Standard operating procedures for the collection, preparation, storage and release of FMT are established at BiomeBank. All processes regarding BiomeBank FMT are conducted within a comprehensive quality control system in line with TGO 105 and principals of GMP.

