### Blinding

Stage 1: No blinding (open label).

Stage 2: This will be a double-blind trial. If a participant reaches the primary endpoint (development of severe diarrhoea within 3 weeks post HSCT) investigators will be unblinded. If the participant is receiving placebo, they will be given a rescue course of open-label FMT (30–36 capsules taken over 5–6 days, i.e. 6 capsules, 3 BD). This innovative design enables the evaluation of the therapeutic efficacy of FMT (i.e. impact of FMT on diarrhoea) without compromising the validity of the trial’s primary objective.

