#### Stage 1 – Safety run in

Safety: Incidence of adverse events (AEs) assessed using the NCI CTCAE v5.0 (when in patient) with focus on treatment emergent adverse events, i.e. those identified to be related to the IP. AEs will be assessed from the time of starting the first course of FMT until 1 month after completion of the second FMT course. These will be assessed daily if the participant is admitted, and weekly when discharged. When an out-patient, assessments will be performed weekly by a member of the study team (phone call to participants). The Safety Monitoring Committee will be responsible for assigning AEs to either the HSCT treatment or IP. If the AE is deemed as probably or definitely related to the IP, they will be defined as a TE-AE.

Adherence/feasibility: Adherence will be defined by the proportion of participants that complete full course of FMT defined by the number of returned (unused) capsules and from participants’ diaries. The IP will be deemed feasible if participants take at least 75% of each course (pre- and post-HSCT).

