##### Exploratory outcomes

Gut microbiota composition assessed using microbial genomic sequencing performed on longitudinal stool samples.Plasma short chain fatty acid concentrations assessed in longitudinal blood samples.Plasma citrulline (biomarker of mucosal barrier injury) assessed in longitudinal blood samples.Salivayr metabolome and microbiome.

Safety and adherence will continue to be assessed as per Stage 1.

See Table 3 for study assessment schedule.

**Table 3 Tab3:** Study assessment schedule

Assessment	Before prophylactic FMT	After prophylactic FMT	Day of HSCT (day 0)	During in-patient stay	Before recovery FMT	After recovery FMT	Day + 21	1 month after
Patient demographics								
Comorbidities								
Medications								
Diagnosis/treatment details								
ECOG performance status								
Adherence								
Bristol stool chart (BSC)			Daily					
Frequency			Daily					
Body weight				2-3x weekly while an in-patient				
Symptom burden			*	*	*	*		*
Adverse events ^								

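### Representatives of the product's manufacturer sit on the committee that decides which adverse events count as product-related, and their optional participation is not barred for that decision

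*Protocol article*

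**What the plan says.** Under the heading Safety and data monitoring, the protocol article says that the Safety Monitoring Committee will include "Site PIs.Chief investigator.Head of Haematology.BiomeBank representative(s"). The section Preparation of FMT shows BiomeBank's role as maker of the product: "Standard operating procedures for the collection, preparation, storage and release of FMT are established at BiomeBank".

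The section Stage 1 – Safety run in gives the committee its main task: "The Safety Monitoring Committee will be responsible for assigning AEs to either the HSCT treatment or IP". The result of that judgement is the safety endpoint: "If the AE is deemed as probably or definitely related to the IP, they will be defined as a TE-AE". The end of the Exploratory outcomes section carries this into the randomised stage: "Safety and adherence will continue to be assessed as per Stage 1". The section Data analyses and synthesis then compares treatment-related AEs between arms.

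On attendance, Safety and data monitoring states: "Participation by the trial statistician and BiomeBank representative will be optional". It also states: "All discussions about a participant and/or their data, once they are enrolled, will be in a de-identified manner". The committee has discretion to stop the trial or withhold the product, taking into account how the event relates to the product. It also reviews Stage 1 before Stage 2 enrolment opens.

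Stage 1 is open-label. Stage 2 is double-blind, with an exception in the Blinding section: "If a participant reaches the primary endpoint (development of severe diarrhoea within 3 weeks post HSCT) investigators will be unblinded".

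**The concern.** After an autologous transplant, infection, fever and gastrointestinal events are expected whether or not FMT is given. The Background section lists infection and diarrhoea among the transplant toxicities, and also names infection through bacterial translocation as the perceived risk of FMT in this setting. The same event can therefore plausibly be assigned either way, and the TE-AE rate depends on who decides.

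The manufacturer has a direct interest in the answer. If its representatives take part in the causality decision, the TE-AE count, the review after the five open-label participants and any later conclusion that the product is safe are open to the criticism that an interested party helped set the endpoint. The criticism has most force where the arm is known when the decision is made, so the question is how far the stated safeguards hide it.

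**Working it through.** This is mainly a matter of reading the sections together. One calculation shows how often the Stage 2 blind is lifted by design.

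**1. Chain of responsibility.** BiomeBank makes the product (Preparation of FMT). Its representatives are listed committee members (Safety and data monitoring). The committee assigns causality, and causality defines a TE-AE (Stage 1 – Safety run in). The same process applies in Stage 2 (Exploratory outcomes). None of these sections separates the manufacturer from the causality decision.

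**2. Stage 1.** All five participants receive FMT openly, so blinding gives no protection.

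**3. Stage 2 arm sizes.** Inputs from Participants and study recruitment and from Randomisation: placebo rate 0.80, FMT rate 0.40, alpha 0.05 (two-sided assumed), power 80%, allocation 2:1. With k = 2 and pooled rate (0.8 + 2 × 0.4)/3 = 0.533, the placebo arm size is

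n = [1.96 × √(1.5 × 0.533 × 0.467) + 0.842 × √(0.8 × 0.2 + 0.4 × 0.6/2)]² / 0.4²
= [1.96 × 0.611 + 0.842 × 0.529]² / 0.16 ≈ 16.9, rounded up to 17.

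This gives 17 placebo + 34 FMT = 51, the protocol's figure (power 80.3%).

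**4. Expected number unblinded.** Unblinding follows the primary endpoint in either arm:

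- Placebo: 0.8 × 17 = 13.6
- FMT: 0.4 × 34 = 13.6
- Total: 27.2 of 51, or 53%

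If FMT had no effect and both arms ran at 80%, it would be 0.8 × 51 = 40.8.

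**5. Does attribution continue after unblinding?** The primary endpoint can occur up to 3 weeks after HSCT. AEs are followed until 1 month after the second course. That course starts after HSCT and lasts 14 days (Table 2), so for a participant who completes it, follow-up ends no earlier than about 14 + 30 = 44 days after HSCT, against 21 days for the endpoint. A participant unblinded at the endpoint therefore still has AEs to be collected and attributed.

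**6. De-identification.** As worded, it concerns the participant's identity. The text does not say that it hides the arm.

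The 27 counts participants whose arm becomes known to investigators. It does not count attributions made with that knowledge, which the document does not allow one to estimate.

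**The case against.** The strongest case against is that safeguards exist and that the article is a condensed account. While the arm is hidden, an assessor cannot selectively move FMT events to the transplant; any leniency falls on placebo participants as well. Discussions are de-identified. BiomeBank's participation is optional, which may simply mean that it need not take part. The membership list says who the committee will include and may not be exhaustive, and voting and recusal rules commonly sit in a charter.

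Much of this stands. Blinding does limit arm-specific bias in Stage 2. It does not cover Stage 1 or attributions made after the endpoint, and even blinded leniency would lower the absolute TE-AE rate in both arms. A charter may already require recusal, but the article itself fixes both the membership and the task, and it leaves the manufacturer free to take part.

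Three stronger readings are tempting and are not supported.

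- **One reclassified event would decide the safety test.** At 34 v 17, the chi-squared test does move from p = 0.065 (6 v 0) to p = 0.044 (7 v 0). That is true of any small 2×2 table near its threshold, whoever sits on the committee. Fisher's exact test gives p = 0.080 at 7 v 0. The protocol states no expected TE-AE rate and ties no safety conclusion to p < 0.05.
- **Site PIs are unsuitable assessors as such.** Nothing in the document shows this. The difficulty is knowledge of the arm, which is specific to the participant.
- **The manufacturer can time its attendance to contested cases.** The text does not say who exercises the option, and the sentence follows one on individual participants, so its scope is unclear.

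**Conclusion.** The point holds as a modest governance weakness in the safety endpoint. The manufacturer's representatives are listed on the body that assigns causality and may withhold the product or stop the trial, and making their participation optional does not keep them out of those decisions. The blind does not fully cover the gap: it is absent in Stage 1 and lifted for an expected 27 or so of 51 participants in Stage 2, with AE follow-up still running.

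The figure of 27 assumes the protocol's own 80% and 40% rates and 34 v 17 participants. The concern about attribution also assumes that the unblinded investigators include committee members, which is likely because the site PIs and chief investigator are listed, but is not spelled out. No bias is shown to have occurred, and its size cannot be estimated from the document. The primary efficacy analysis is unaffected. The change is worth making because it costs almost nothing.

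**What to change.** In Stage 1 – Safety run in and in Safety and data monitoring, state that manufacturer representatives may supply product-quality information, do not vote on causality, withholding or stopping, and leave the meeting for those decisions, in both stages.

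For Stage 2, add that causality is assigned by existing committee members who have not been unblinded for that participant, and is recorded before any unblinding where possible. For this to work, the Blinding section should say which investigators learn the arm, so that some members stay blind; with two sites named, members from the other site could do so. The treating clinician may still be consulted. Arm-blind assessment is not possible in Stage 1, where recusal is the available protection.

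The cost is a few sentences and slightly more committee administration, using people already on the committee. If a charter already contains these rules, one sentence referring to it is enough.

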#### Dissemination plan

Results will be published in appropriate peer-reviewed journals and presented at national and international scientific meetings (e.g. Haematolgy Society of Australian and New Zealand, Multinational Association for Supportive Care in Cancer, Clinical Oncology Society of Australia, International Human Microbiome Congress, American Society for Clinical Oncology, European Bone Marrow Transplantation Congress, European Society of Medical Oncology, American Society of Haematology). We will also work with community organisations such as Leukaemia Foundation and Myeloma Australia to ensure these data are communicated with consumers.

## Discussion

Fecal microbiota transplantation (FMT) technology is rapidly evolving in its science and form, facilitating its use in vulnerable populations that lack the protective benefits of a healthy microbiome or where traditional methods of administration are complex, or even, contraindicated. FMT is recognised to be beneficial in HSCT recipients, yet its use in the acute phases of HSCT, when its benefits are likely maximised, has been limited. The HSCT-BIOME study will be the first to investigate the efficacy of peri-HSCT delivered oral capsule FMT against the primary outcome measure of severe diarrhoea post HSCT. This study will thus clarify if pre-HSCT delivered FMT can promote microbial resilience against insults experienced during HSCT, and whether post-HSCT delivered capsule FMT can be safely and feasibly administered to immunocompromised patients to improve treatment outcomes.

Whilst our study design remains largely aligned with existing studies, there are unique aspects of the study including the use of peri-HSCT FMT and provision of an encapsulated product. Of particular interest is the decision to include open-label, rescue FMT in situations where participants in the placebo arm reach the primary endpoint. This not only increases participant satisfaction, through accessing the intervention irrespective of randomisation, but also enables both the prophylactic and therapeutic efficacy of FMT to be explored in a single cohort, thus increasing the efficiency and value of the trial.

While the HSCT-BIOME trial primarily focuses on symptoms and clinical outcomes, it will also have a strong mechanistic focus on minimising the depth and duration of GI injury to reduce the sequaelae of associated adverse effects (e.g. infection, malnutrition). Longitudinal collection of blood and stool biospecimens throughout the study will allow for more in depth exploration of the physiological effects induced by the intervention (changes to the microbiome, intestinal health, and reconstitution of immunity), which may be useful in the identification of key attributes related to the host and the FMT that dictate response. These insights will be used to develop next generation, engineered FMT products specifically designed for HSCT.

## Data Availability

No datasets were generated or analysed during the current study.

## Abbreviations

AE: Adverse event
ANC: Absolute neutrophil count
BSC: Bristol stool chart
BSI: Blood stream infection
CALD: Culturally and Linguistically diverse
CDI: Clostridium difficule infection
CRF: Clinical Record Forms
ESAS-r-CS: Revised Edmonton Symptom Assessment System including constipation/sleep
FMT: Faecal microbiota transplantation
GCP: Good clinical practice
GVHD: Graft versus Host Disease
HSCT: Haematopoietic stem cell transplantation
IP: Investigation product
MDB: Multidrug resistant bacteria
NCI CTCAE: National Cancer Institute’s common terminology criteria for adverse events
PI: Principal investigatorRedCAP: Research Electronic Data Capture
SAE: Serious adverse event
SCFA: Short chain fatty acid
SSL: Secure sockets layer
TBI: Total body irradiation
TE-AE: Treatment emergent adverse event
TGA: Therapeutic Goods Administration
